##### HISQUI_19_

The HISQUI_19_ is a 19-item questionnaire to quantify the degree of self-perceived auditory benefit experienced by CI users in everyday communication situations (Amann and Anderson, 2014). The 19 items are rated on a 7-point Likert scale ranging from always (99%) to never (1%). To calculate the overall score the corresponding numerical value of each item (from always = 7 to never = 1) is added. Uncompleted items and the response option “not applicable” correspond to 0 in this calculation. A total score of less than 30, 30–59, 60–89, 90–109, and 110–133 is respectively classified as a very poor, poor, moderate, good, and very good self-perceived auditory benefit. The validated Dutch version of the questionnaire is used (Mertens et al., 2015). The 19 items of this questionnaire are listed and added as Supplementary Material available online.

#### Questionnaires

##### NCIQ

The Nijmegen Cochlear Implant Questionnaire (NCIQ) is a Dutch self-assessment health-related quality of life instrument developed for use in CI users (Hinderink et al., 2000). The questionnaire consists of 60 questions divided into three principal domains: Physical, Psychological, and Social. The first domain comprises three subdomains, namely Basic sound perception, Advanced sound perception, and Speech production. The Psychological domain contains the subdomain Self-esteem and the Social domain handles questions about Activity limitations and Social interactions. Each subdomain covers 10 statements. Each statement is rated on a 5-point Likert scale ranging from “Never” to “Always” (Statement 1–55) or from “No” to “Quite well” (Statement 56–60). A list of the statements of this questionnaire is added as Supplementary Material available online.

##### SSQ12

The SSQ12 (Noble et al., 2013) is a short form of the Speech, Spatial, and Qualities of Hearing scale (Gatehouse and Noble, 2004). It is developed for use in clinical research and rehabilitation settings to measure a range of hearing disabilities across several domains such as speech in noise, speech in speech, localization, distance, and movement, segregation and listening effort. The 12 items of this questionnaire are rated on a visual analog scale from 0 to 10 and the overall score is calculated by taking the average of the scores on these 12 items. The full questionnaire is added as Supplementary Material available online.

##### HADS

To detect states of depression and anxiety the Hospital Anxiety and Depression Scale (HADS) is used (Zigmond and Snaith, 1983). This self-assessment questionnaire consists of seven items in the subscale Depression and seven items in the subscale Anxiety and distinguishes clearly between both emotional disorders. A list of the items of the HADS are available online as Supplementary Material.

#### Interview

In a semi-structured interview, the following topics are covered: Hearing loss, Education and profession, Rehabilitation, Self-reliance and Family. A detailed overview of the different items discussed in the interview is given in Table 3.

**Table 3 T3:** **The five main topics and the different items discussed in the semi-structured interview**.

**Hearing loss**	**Education and profession**	**Rehabilitation**	**Self-reliance**	**Family**
Onset	Years of formal education	Preoperative	Housing	Birth order
Etiology	Degree of studies	Postoperative	Mobility	Number of (grand) children
Device use	Profession		Eating and cooking	Number of siblings
Tinnitus			Personal hygiene	
			House holding	
			Sense of danger	
			Communication	
			Activities	
			Participation in society	
			Mental and fysical health	

### Stepwise procedures

The minimal outcome measurements (MOM), consisting of unaided and aided audiometry, speech audiometry in quiet, speech audiometry in noise and the HISQUI_19_, are part of the standard clinical practice of care and follow-up of CI users in the Antwerp University Hospital. These measurements are performed preoperatively, at three, 6 and 12 months after activation of the speech processor and from then on annually. If the subject agrees to participate in the study, the RBANS-H, the semi-structured interview and the three questionnaires, NCIQ, SSQ12 and HADS, are added to the standard follow-up procedure preoperatively, at 6 and 12 months after activation of the speech processor and annually onwards, without additional appointments.

The three questionnaires are sent by mail to the participants 2 weeks prior to the appointment. The participants are asked to fill out these questionnaires at home and return them at the time of the testing. During the appointment the minimal outcome measurements are performed first, in the previously listed order. The MOM is followed by the cognitive assessment and the semi-structured interview. At the end of the appointment the examiner verifies whether the questionnaires are fully completed by the participant. The complete testing takes approximately one and a half to two hours. In the case of a postoperative appointment, the speech processor is fitted, if needed, prior to the MOM.

### Ethics

This study is carried out in accordance with the recommendations of the ethics committee of the Antwerp Univerity Hospital with written informed consent from all subjects. All subjects give written informed consent in accordance with the Declaration of Helsinki. The protocol was approved by the ethics committee of the Antwerp University Hospital (protocol number 15/17/181) on June 15th, 2015.

### Statistics and anticipated results

The sample size calculation is based on the primary outcome variable, RBANS-H total score. A sample of 19 persons is needed to obtain 80% power using a paired *t*-test to detect a Cohen's d of 0.7 at an alpha level of 0.05. Due to the age of the study population and the duration of the longitudinal study, a 20% dropout rate is taken into account. The targeted total sample size is therefore adjusted to 25.

Descriptive statistics will be used to summarize the mean/median, standard deviation, and possible ceiling or floor effects of the different variables. The effect of the treatment on the primary outcome will be modeled using linear mixed models. *Post-hoc* comparisons will be carried out to test for differences in outcomes between the different time points, using Tukey's correction for multiple comparisons. In order to avoid statistical threats such as regression toward the mean, data will be analyzed as a whole, and not split up into groups based on the cognitive performances. The most recent version of IBM SPSS Statistics (IBM; Armonk, NY) and R (R Development Core Team; Vienna, Austria) will be used for the analyses.

Given the previous study conducted by Mosnier et al. (2015) it is hypothesized that, in general, the cognitive abilities of the older adults will increase at 6 and12 months after implantation. After this initial increase a gradual decrease in cognition is expected, similar to the age-related cognitive decline in normal hearing subjects. In other words, the authors expect the RBANS-H total percentile to increase during the first year after implantation, i.e., the hearing impaired participants will catch-up with the normal hearing norm group of the RBANS, and stabilize over the next nine years, i.e., the hearing impaired participants will show a cognitive decrease similar to the norm group.

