### Primary outcome measurement: RBANS-H

The primary outcome measurement is the change in cognitive capabilities following implantation, as measured by means of the Repeatable Battery for the Assessment of Neuropsychological Status (RBANS, Randolph et al., 1998), adjusted to test Hearing impaired subjects (RBANS-H). The RBANS assesses five cognitive domains, i.e., *Immediate Memory, Visuospatial/constructional, Language, Attention*, and *Delayed Memory* (Table 2). The test consists of 12 subtests and the score on each subtest contributes to one of the five domains. The Dutch version of the original English RBANS is obtained by the process of forward-backward translation. In order to test subjects with a severe hearing impairment a number of adjustments to the standard RBANS had to be made (Phillips, 2016). The administration of the test is accompanied by the use of a PowerPoint presentation shown on an external computer screen connected to a laptop. By means of this presentation all the oral instructions are supported by written explanations to ascertain that the subject understands the instruction even though he or she does not hear what is being said. In addition, the stimuli in the subtests *List Learning, Story Memory, Digit Span*, and *List Recognition* are not only presented auditorily but also visually, making it possible to test the subject in the same reliable way before and after implantation. All the adjustments were made in accordance to the guidelines of the RBANS, as discussed in the manual on page 15 “Testing Examinees With Physical or Language Impairments” (Randolph, 2012). The RBANS was ordered on the website of Pearson Clinical (http://www.pearsonclinical.com).

**Table 2 T2:** **The five cognitive domains and twelve subtests of the RBANS**.

**Immediate memory**	**Visuospatial/ constructional**	**Language**	**Attention**	**Delayed memory**
(1) List Learning	(3) Figure Copy	(5) Picture Naming	(7) Digit Span	(9) List Recall
(2) Story Memory	(4) Line Orientation	(6) Semantic Fluency	(8) Coding	(10) List Recognition
				(11) Story Recall
				(12) Figure Recall

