The current study shares a comparable purpose as the study of Mosnier et al. (2015). Therefore, the study protocol of the current study is similar to the study protocol of Mosnier et al. (2015) with regard to the overall study design: both are prospective, longitudinal cohort studies concerning the cognitive functions of hearing impaired older adults with fixed test moments before implantation and at 6 and 12 months after implantation. Cognition, audiological performances and quality of life are investigated in both studies. However, the current study aims to investigate the cognitive trajectory not merely in the short term, but also in the long term, up to 10 years after implantation. Furthermore, in order to detect mild cognitive impairments at an early age, subjects of 55–65 years old are included as well. Finally, the major added value of the current study is that it does not make use of a composite test battery, but that it uses instead a comprehensive test, the RBANS-H, a cognitive assessment adjusted for use in hearing impaired subjects. This test makes it possible to calculate one total score of overall cognition, and also provides the opportunity to calculate the index scores per domain *Immediate Memory, Visuospatial/constructional, Language, Attention*, and *Delayed Memory*. The RBANS is sensitive to detect mild cognitive impairments in individuals aged 12–89 providing extended normative data per age category (12–13, 14–15, 16–19, 20–39, 40–49, 50–59, 60–69, 70–79, 80–89). The test effectuates the possibility to differentiate in a wide range from normal to moderately severe cognitive impairments. Another major advantage of the RBANS is that this test has a good sensitivity to change with 90 and 95% confidence intervals provided for the total score as well as each index score. The test is validated and available in English and Spanish, and easy to translate to other languages through the process of forward-backward translation. It takes around 30 min to administer the RBANS.

In contrast to the RBANS, the screening test Montreal Cognitive Assessment (MoCA) merely takes 10–15 min to administer and can be downloaded online for free (http://www.mocatest.org). However, screening tests such as MoCA are less sensitive and only differentiate between normal and abnormal cognitive function. In Table 4 a summary is given of the advantages and the limitations of the MoCA and the RBANS.

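### The 80% power is computed for one unadjusted paired t-test, but the only time-point comparisons described are Tukey-corrected, and no primary contrast is named

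*Protocol article*

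**What the plan says.** All of this comes from the protocol article.

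- **Primary outcome** (Primary outcome measurement: RBANS-H): "The primary outcome measurement is the change in cognitive capabilities following implantation". No time point is attached to the change.
- **Sample size** (Statistics and anticipated results): "The sample size calculation is based on the primary outcome variable, RBANS-H total score". The number and the test, a t-test on pairs, come next: "A sample of 19 persons is needed to obtain 80% power using a paired". The assumed effect and significance level are given as follows: "to detect a Cohen's d of 0.7 at an alpha level of 0.05". For losses, "a 20% dropout rate is taken into account", and the enrolment figure reads: "The targeted total sample size is therefore adjusted to 25".
- **Analysis** (same section): the primary outcome is modelled with linear mixed models. Differences between time points are then tested in comparisons labelled post-hoc, "using Tukey's correction for multiple comparisons". The section does not say whether the primary inference is the model's time effect or one of the pairwise contrasts.
- **Schedule** (Study protocol and Table 1): RBANS-H before implantation, at 6 and 12 months, then yearly. The Discussion extends follow-up beyond the short term: "but also in the long term, up to 10 years after implantation".
- **Hypothesis** (Statistics and anticipated results): a rise at 6 and 12 months, then a stable percentile.

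**The concern.** The sample size paragraph and the analysis paragraph describe different tests. The first assumes two time points compared once at 0.05. The second compares time points only under a Tukey correction, which raises the critical value, and the sample size calculation makes no allowance for that.

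The expected result is specific in direction and timing: a gain by 6 and 12 months. A reader will naturally attach the 80% to the 12-month change, but if that change is judged by its Tukey-adjusted contrast, the 80% was not calculated for it. In addition, if the Tukey family grows with each annual visit, the threshold for the same 12-month contrast rises as follow-up continues. A non-significant 12-month result could then come from the correction rather than from the data.

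**Working it through.** **1. Inputs.** d = 0.7, alpha 0.05, n = 19, 25 enrolled and 20% dropout, all from Statistics and anticipated results. Visits: preoperative, 6 months, 12 months and years 2 to 10, so 3 + 9 = 12 time points and 12 × 11 / 2 = 66 pairs. The article gives no SD and no within-subject correlation, so d is taken as mean change divided by SD of change, the same for every pair. Sidedness is not stated.

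**2. The plan's own figure.** Power of a two-sided paired t-test is taken from the noncentral t with df = n − 1 and ncp = 0.7√n.

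- n = 18: 79.9%.
- n = 19: ncp = 0.7 × 4.359 = 3.05, critical t 2.101, power 82.3%.

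So 19 is the smallest n with at least 80%, and the stated number reproduces as a two-sided test. A one-sided test would need only 15. For dropout, 19 / 0.8 = 23.75, and 25 enrolled leaves 25 × 0.8 = 20, so 25 is adequate for the test it was computed for.

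**3. The same contrast under Tukey.** For k visits the critical value is c = q(0.95; k, df)/√2, where q is the studentized range quantile and df = (n − 1)(k − 1). The ncp is unchanged. Complete data and sphericity are assumed. Power is for one named pair:

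| Evaluable n | ncp | Unadjusted paired t | Tukey, 3 visits (c) | Tukey, 12 visits (c) |
|---|---|---|---|---|
| 19 | 3.05 | 82% | 72.6% (2.444) | 40.2% (3.308) |
| 20 (25 less 20%) | 3.13 | 84% | 75.2% (2.439) | 43.3% (3.306) |
| 25 (no dropout) | 3.50 | 92% | 85.6% (2.418) | 58.1% (3.298) |

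Adding only the first annual visit (4 visits) at n = 19 gives c = 2.651 and power 65.5%. If the error df is n − 1 instead of pooled, the n = 19 figures fall to 68.9% (3 visits) and 30.0% (12 visits).

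**4. Number needed for 80% on one named pair.** Three visits: 22 gives 79.9% and 23 gives 82.0%, so 23 completers, or 23 / 0.8 = 28.75, rounded up to 29 enrolled. Twelve visits: 35 completers, or 35 / 0.8 = 43.75, rounded up to 44 enrolled.

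**5. Other possible primary tests.** Suppose every post-implant mean is 0.7 above baseline.

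- Overall time-effect F test: 86.6% (3 visits) and 78.3% (12 visits) at n = 19; 88.5% and 81.0% at n = 20.
- At least one significant baseline-to-post Tukey contrast, by simulation at n = 19: about 85% with 3 visits and about 85% with 12.
- A significant change at 6 or 12 months within the 12-visit family, same simulation at n = 19: about 55%.

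If instead the gain is 0.35 at 6 months and 0.7 at 12 months, the three-visit F test has 74.8% power at n = 19 and 77.3% at n = 20.

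**The case against.** A reader might infer that the planned primary test has only 73% or 40% power. The article does not support that. It labels the Tukey comparisons post-hoc, places them after a mixed model, and does not name the primary test. If the overall time effect is primary, power under a sustained gain is near 80% or above.

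The n = 19 row is also below what the plan provides for. Twenty-five are enrolled, and the dropout allowance is justified partly by the length of follow-up, so it need not be used up by 12 months. A mixed model also uses incomplete series. With three visits the realistic range is therefore about 75% to 86%, and 80% is reached from 23 evaluable, so there may be no shortfall. Sizing on a paired t-test is a common simplification, the Conclusion calls the study exploratory, and a fuller analysis plan may name the contrast.

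Most of this stands and limits the point. Three things remain. First, both the unadjusted test and the Tukey correction are stated in the article, so their mismatch is not an omission left to another document. Second, an overall time effect shows neither direction nor timing, whereas the hypothesis specifies both. The roughly 85% chance of some significant baseline-to-post contrast counts changes at any visit to year 10, and it does not protect the 6- or 12-month result. Third, if one family spans all 12 visits, power for a named pair is below 80% even with no dropout (58%).

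**Conclusion.** The concern holds in a limited form. The arithmetic behind 19 and 25 is sound for one unadjusted two-sided paired t-test, but the article describes no such test among its comparisons of time points and names no primary contrast.

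For a specific contrast such as baseline to 12 months, with 20 to 25 evaluable, Tukey power is about 75% to 86% over three visits and about 43% to 58% if one family covers 12 visits. These figures assume d = 0.7 per SD of change for the pair concerned, sphericity and complete data. The 12-visit figures also assume that a single Tukey family spans the whole ten years, which the article does not state. It would be wrong to conclude that the study's overall ability to show a post-implant change falls to 40%.

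This is worth correcting because it is the only power figure the article gives. It is not critical, given that the study presents itself as exploratory.

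**What to change.** Name the change from baseline to 12 months in RBANS-H total score as the single primary contrast. Estimate it in the mixed model and test it once at two-sided 0.05, outside the Tukey family. Treat the other time-point comparisons as secondary, either Tukey-adjusted among themselves or reported as estimates with confidence intervals. The stated 19 and 80% then hold, provided at least 19 are evaluable at 12 months.

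If Tukey is kept for that contrast, restate its power with the assumptions: at 20 completers, about 75% for a three-visit family and about 43% for a 12-visit family. Say which visits make up the family.

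The first option costs one sentence and needs no extra patients or visits. Its price is that the other comparisons, including 6 months and the long-term visits, carry less inferential weight.

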### Data management

In order to enter and store the data in a secure, efficient, and clean manner, OpenClinica LLC is used. This is a software package for electronic data capture and data management developed for clinical research. This database is protected by a combination of user IDs and passwords and is only accessible to the principal investigators. Validation checks (e.g., range checks) for data values are programmed in order to minimize the number of mistakes while entering data. The information collected from this study is kept confidential. Individual information and results in the database are coded and only the researcher knows which code refers to which subject. The information is not shared with or given to anyone.

## Discussion

The primary aim of this prospective, longitudinal cohort study is to investigate the cognitive profile in older adults aged 55 or more with a profound hearing loss before and after cochlear implantation, both in the short and the long term. Secondly, due to the extensive audiological, cognitive, and qualitative examination, the current study also provides the opportunity to explore the relationship between the cognition, audiometric performances, quality of life and self-reliance in these patients. Before these research questions can be tackled, the feasibility and the validity of the RBANS-H to test hearing impaired older adults will be evaluated with regard to the following three questions: Are the written instructions clear to the participants? Do the modifications in the subtests *List Learning, Story Memory, Digit Span*, and *List Recognition* make it possible for the patients to fulfill these subtests? Is the RBANS-H sufficiently sensitive to detect changes in this population?

To the best of our knowledge, only one study conducted by Mosnier et al. (2015) investigated the effect of cochlear implantation on cognition in 94 subjects aged 65 or older. They used a test battery comprising six tests: Mini-Mental State Examination (MMSE) (Folstein et al., 1975; Derouesne et al., 1999; Lechevallier-Michel et al., 2004), 5-word test (Grober et al., 1988; Dubois et al., 2002; Cowppli-Bony et al., 2005), clock-drawing test (Solomon et al., 1998), verbal fluency test (Cardebat et al., 1990), d2 test of attention (Brickenkamp and Zillner, 1990), and trail making test (Tombaugh, 2004). By means of these tests, attention, memory, orientation, executive function, mental flexibility and fluency were assessed. These tests were performed preoperatively and at 6 and 12 months postoperatively. Mosnier et al. (2015) concluded that hearing rehabilitation through cochlear implantation results in improvements of cognitive abilities: more than 80% of the subjects with the poorest cognitive scores preoperatively improved their cognitive function significantly one year after implantation. In contrast, the cognitive capabilities of the majority of the subjects with normal scores preoperatively did not change significantly postoperatively. However, in 24% of these subjects a slight but significant decline in cognitive function was observed after the implantation.

The current study shares a comparable purpose as the study of Mosnier et al. (2015). Therefore, the study protocol of the current study is similar to the study protocol of Mosnier et al. (2015) with regard to the overall study design: both are prospective, longitudinal cohort studies concerning the cognitive functions of hearing impaired older adults with fixed test moments before implantation and at 6 and 12 months after implantation. Cognition, audiological performances and quality of life are investigated in both studies. However, the current study aims to investigate the cognitive trajectory not merely in the short term, but also in the long term, up to 10 years after implantation. Furthermore, in order to detect mild cognitive impairments at an early age, subjects of 55–65 years old are included as well. Finally, the major added value of the current study is that it does not make use of a composite test battery, but that it uses instead a comprehensive test, the RBANS-H, a cognitive assessment adjusted for use in hearing impaired subjects. This test makes it possible to calculate one total score of overall cognition, and also provides the opportunity to calculate the index scores per domain *Immediate Memory, Visuospatial/constructional, Language, Attention*, and *Delayed Memory*. The RBANS is sensitive to detect mild cognitive impairments in individuals aged 12–89 providing extended normative data per age category (12–13, 14–15, 16–19, 20–39, 40–49, 50–59, 60–69, 70–79, 80–89). The test effectuates the possibility to differentiate in a wide range from normal to moderately severe cognitive impairments. Another major advantage of the RBANS is that this test has a good sensitivity to change with 90 and 95% confidence intervals provided for the total score as well as each index score. The test is validated and available in English and Spanish, and easy to translate to other languages through the process of forward-backward translation. It takes around 30 min to administer the RBANS.

In contrast to the RBANS, the screening test Montreal Cognitive Assessment (MoCA) merely takes 10–15 min to administer and can be downloaded online for free (http://www.mocatest.org). However, screening tests such as MoCA are less sensitive and only differentiate between normal and abnormal cognitive function. In Table 4 a summary is given of the advantages and the limitations of the MoCA and the RBANS.

**Table 4 T4:** **A schematic representation of the comparison between MoCA and RBANS**.

	**MoCA**	**RBANS**
Languages	>50 languages	English and Spanish
Public domain?	Yes	No
Duration	10–15 min	±30 min
Differentation in level of cognition	Normal *OR* mild cognitive impairment (screening)	Normal *TO* moderately severe dementia (scaled scores and percentiles with extensive normative data)
Index scores per cognitive domain	No	Yes (5)
Sensitivity to change	Limited	Good (+90 and 95% confidence intervals for the overall score and each index score)

Adding visual support to the subtests *List Learning, Story Memory, Digit Span*, and *List Recognition* was considered necessary to test the hearing impaired subjects in a reliable and identical manner before and after implantation and to ascertain that a possible improvement on the cognitive test cannot be attributed to the improved hearing with the CI (Phillips, 2016). According to the study of Delogu et al. (2009), the addition of visual stimulation in a verbal auditory memory task has no significant effect on the number of words repeated by the subjects. Since the auditory presentation is dominant in the case of verbal stimuli and there is no additional benefit from a bimodal (written and spoken) encoding of words, the modifications performed in this study are hypothesized to have little impact on the results. Nevertheless, these modifications may still have a small effect on the test scores and may invalidate the rigid use of the norms. By exploring the change in test and index scores, rather than the test and index scores *per se*, the effects of the modifications are reduced to the minimal.

In the proposed study, no control group is included. The discussion concerning the control group has to be situated in the background of increasing the level of evidence-based medicine for surgical procedures. Due to the absence of a control group, the effect of cochlear implantation on the cognition can, theoretically, not be separated from any change in cognition that occurs over time and no conclusion with regard to the causality of any observed changes can be rigorously taken. In order to answer the causality question whether cochlear implantation affects cognition and whether cochlear implantation can decelerate the age-related cognitive decline a different study design is required, such as a randomized clinical trial design. Obviously, due to ethical restrictions and the invasive nature of the intervention, it is impossible to randomly assign subjects, who all meet the criteria for reimbursement of cochlear implantation, to either the interventional or to the non-implanted control group.

Another option is a randomized delayed-start design, in which half of the participants are randomly assigned to either the immediate-intervention group or the delayed-intervention group. The Belgian national criteria for reimbursement of cochlear implantation are stricter than the internationally accepted minimal criteria for reimbursement. As a consequence, in the current study subjects with more severe hearing losses are recruited than would be the case in other countries. Even more postponing the implantation of a given participant would be unethical and would not be accepted by the patient, making it impossible to include the necessary number of subjects in a reasonable amount of time.

Furthermore, even without a random assignment of each participant to either the control group or the interventional group, the inclusion of a control group involves a number of problems which may either way bias the results. The subjects in the control group would ideally have the same audiological profile as the subjects in the interventional group but must not be implanted in the next 10 years. Since these subjects, like the subjects in the interventional group, do meet the criteria for reimbursement of cochlear implantation, the reason why they will not be implanted after all, may be also the reason why they should not be included in a control group, for instance because of a severe cognitive dysfunction or a complex health problem.

Therefore, the present study does not include a control group, but neither aims to point out whether cochlear implantation can decelerate the age-related cognitive decline or not. Instead, the study's purpose is to explore the cognitive profile of profoundly hearing impaired older adults before and after cochlear implantation using a comprehensive cognitive assessment and to investigate the relationship between cognition, audiometric performances, quality of life and self-reliance. Moreover, the current study may incite the design of more studies concerning cochlear implantation and cognition, such as studies assessing cognitive function in severely hearing impaired older adults who are not implanted and comparative simultaneous multicenter case-control studies taking advantage of the international differences between the criteria for reimbursement of cochlear implantation.

